## Abstract

**Background:**

In recent years, the rising incidence and comorbidity of major depressive disorder (MDD) and non-suicidal self-injury (NSSI) among adolescents have emerged as a critical global public health challenge. Existing interventions often face limitations such as low patient willingness and poor adherence, restricting their effectiveness. This situation creates an urgent need to explore effective and acceptable interventions. Therapeutic Horticulture (TH) is a novel treatment that uses plant cultivation and related gardening activities as a therapeutic medium. It engages patients in planting, nurturing, and harvesting plants to achieve therapeutic effects. While it shows promise for adolescents with MDD, its efficacy specifically in adolescents with comorbid MDD and NSSI remains unclear. Therefore, this trial aims to evaluate the effects of TH on NSSI and psychosocial functioning in adolescents with MDD.

**Methods:**

This is a single-center, block-randomized, two-arm parallel randomized controlled trial (RCT) will be conducted at the Brain Hospital Affiliated with Guangzhou Medical University, Guangdong, China. Sixty-six participants will be allocated to an intervention or control group via block randomization. Inclusion criteria are (1): diagnosis of MDD and NSSI per DSM-5 criteria; (2) aged 12–18 years; (3) provision of informed consent; and (4) adequate comprehension, communication, and writing abilities. Exclusion criteria include comorbid other mental disorders, history of serious physical illness, receipt of systematic horticultural therapy within the past three months, allergies, or suicidal risk behaviors.The control group will receive treatment as usual. The intervention group will receive TH in addition to treatment as usual for two weeks. The primary outcome is the severity of NSSI. Secondary outcomes include depression, alexithymia, self-efficacy, sleep quality, and loneliness. All outcomes will be assessed at baseline (T_0_) and immediately post-intervention (T_1_).

**Discussion:**

This study will investigate the application of TH in adolescents with comorbid depression and NSSI. The findings may offer a novel treatment option for this population and provide evidence for future clinical interventions and research.

**Trial registration:**

https://clinicaltrials.gov/study/NCT07115381. ClinicalTrials.gov identifier NCT07115381. Registered on 11 August 2025. Protocol version: 1.0, dated 31 October 2024.

## Introduction

1

Adolescent mental health is a critical determinant of lifelong well-being and societal development. Among the various mental health challenges, the co-occurrence of major depressive disorder (MDD) and non-suicidal self-injury (NSSI) presents a particularly complex and urgent public health issue. MDD is a mood disorder characterized by persistent and pervasive low mood, diminished interest or pleasure, and anhedonia. It is often accompanied by symptoms such as appetite loss, sleep disturbances, and difficulty concentrating (1). In severe cases, suicidal ideation and behavior may occur. Of significant concern, a global meta-analysis estimates the prevalence of MDD among adolescents to be approximately 8%, with a rising trend (2).

NSSI refers to the direct and deliberate destruction of one’s own body tissue, through acts such as cutting, burning, scratching, or hitting, that occurs without suicidal intent (3). These behaviors are non-lethal and socially unacceptable. Investigations indicate a global prevalence of approximately 17.7% (4) for NSSI among adolescents, with onset often occurring in early adolescence (5). This behavior is particularly prominent in adolescents with MDD, where its lifetime prevalence can be as high as 52% (6). NSSI poses substantial risks. It increases the risk of suicide among individuals with depression more than seven times (7). Beyond causing physical harm, it can exacerbate psychological distress. According to the 2019 Global Burden of Disease data, NSSI ranks third among causes of disability-adjusted life years in individuals aged 10–24 years, imposing a heavy burden on patients, families, and society (8). The co-occurrence rate of NSSI and MDD is estimated to be between 11% and 15% (9). This complex interaction complicates clinical intervention. Patients with this comorbidity often present with more severe depressive symptoms, poorer treatment response, and higher relapse risk (10). Consequently, effective intervention for NSSI is a critical pathway to improving outcomes in adolescents with MDD.

Current primary interventions for NSSI in adolescents with MDD include pharmacological, physical, and psychological treatments. Pharmacotherapy is widely used but requires consideration of side effects, dependency, and potential increased suicide risk in some adolescents (11). Common physical interventions include repetitive transcranial magnetic stimulation (rTMS) and (Electroconvulsive Therapy, ECT). While preliminary research suggests rTMS may be a promising method, its mechanisms are not fully understood, and robust clinical evidence specifically for NSSI is lacking (12). Some studies have also confirmed that ECT can significantly reduce NSSI in adolescents (13). However, this therapy may be accompanied by a series of adverse effects, such as headache and nausea, and therefore requires cautious use (14). Additionally, some patients and their families are reluctant to accept this treatment, and its efficacy for NSSI remains a subject of debate.

The 2022 UK National Institute for Health and Care Excellence (NICE) guideline on self-harm assessment, management, and relapse prevention emphasizes that interventions for NSSI in adolescents with depression require a comprehensive assessment and treatment of comorbidities and psychosocial factors (15). Evidence-based psychological interventions recommended for NSSI in adolescents with depression include cognitive behavioral therapy (CBT) (16), dialectical behavior therapy (DBT) (17), and acceptance and commitment therapy (ACT) (18) and other interventions. While these therapies show efficacy, they are often constrained by high time and financial costs, specialized requirements, and limited service availability (19). Furthermore, given adolescent developmental characteristics, long-term, single-modality treatments may exacerbate negative emotions, reduce treatment acceptance and adherence, and induce resistance, thereby diminishing therapeutic effects (20). Therefore, exploring effective, integrated, psychologically appealing interventions with minimal side effects is of paramount importance.

Horticultural therapy (HT) is defined by the American Horticultural Therapy Association (AHTA) as therapeutic horticultural activities led by a registered therapist to meet individualized treatment goals (21). Therapeutic horticulture (TH) refers to participation in horticultural activities facilitated by a trained professional, using gardening as a therapeutic means to support program goals (21). The key distinction is that HT requires guidance from a registered therapist, whereas TH can be led by other trained professionals. Both approaches have demonstrated positive effects in mental health rehabilitation (22), and the terms are often used interchangeably in research (23). While HT may yield greater benefits, TH is more feasible for widespread application in settings lacking specialized therapists.

TH is an adjunctive treatment method grounded in horticulture. It integrates multiple disciplines, including rehabilitation medicine, psychology, and sociology. It shows promising application prospects in the field of mental health rehabilitation. Existing evidence indicates that TH can effectively improve depression and anxiety, enhance quality of life and social functioning, and restore hope and confidence in adolescents (24, 25). However, TH interventions in previous studies often lacked a systematic and scientific theoretical framework. With increasing scholarly attention, theoretical research in this field has made progress. For instance, Zhang et al. (26) constructed a healing system framework for TH. This framework uses healing landscapes and activities as its core structure and employs sensory stimulation and structured procedures as its fundamental methods. Its mechanism of action primarily involves a synergistic process of sensory stimulation, emotional responses within psychological mechanisms, and neuroimmune modulation within brain mechanisms, mainly through the five senses. It aims to achieve rehabilitation for patients with mental disorders across four dimensions: positive emotion, functional recovery, skill acquisition, and social interaction. This theory provides a solid foundation for designing targeted TH intervention programs. Compared to traditional medical approaches, TH also offers the advantages of being engaging and having minimal side effects. Despite the considerable therapeutic effects observed for TH in adolescent and depressed populations, research on its application specifically for adolescents with comorbid MDD and NSSI remains extremely scarce.

Based on this rationale, we this designed study as a randomized controlled trial (RCT) to evaluate the effects of TH on NSSI and overall psychosocial functioning in adolescents with MDD. The aim is to explore a gentle and effective intervention method and provide scientific evidence for improving NSSI in adolescents with MDD.

## Methods and analysis

2

### Study design

2.1

This is a single-center, block-randomized, two-arm parallel randomized controlled trial (RCT). The study protocol adheres to the SPIRIT 2025 statement (27). Participants are allocated in a 1:1 ratio to two groups via block randomization. The control group receives treatment as usual (TAU). The intervention group will receive Therapeutic Hrticulture (TH) in addition to TAU. The intervention period is two weeks. Assessments are conducted at baseline (T_0_) and immediately post-intervention (T_1_). The study flowchart is presented in **Figure 1**, and the schedule of enrollment, interventions, and assessments is detailed in **Table 1**.

**Figure 1 f1:**
[figure not shown]
Technology roadmap.

**Table 1 T1:** The schedule of enrollment, interventions, and assessments.

Item	Trial period				
	Enrollment		Post-randomization		Closeout
Time point	-T_1_→ T_0_	T_0_	Week 1	Week 2	T_1_
Enrollment					
Eligibility screen	×				
Informed consent	×				
Randomization		×			
Intervention or comparator					
Intervention group (TAU + TH)		×	×	×	×
Control group (TAU only)		×	×	×	×
Assessments					
Demographic information	×	×			
Disease-related information	×	×			
ASHS		×			×
HAMD-17		×			×
TAS-20		×			×
GSES		×			×
PSQI		×			×
UCLA-LS		×			×
Safety evaluation		×			×
Table of trial completion and early termination	×	×	×	×	×

### Study setting and participants

2.2

#### Study setting

2.2.1

The study is conducted at the Brain Hospital Affiliated with Guangzhou Medical University, a tertiary Grade A psychiatric specialty hospital. All study procedures, including participant recruitment, intervention delivery, and outcome assessments, take place within the closed psychiatric ward of this hospital.

#### Inclusion and exclusion criteria

2.2.2

Participants are included in the study if they meet the following criteria (1): Meet the diagnostic criteria for major depressive disorder (MDD) as defined in the Diagnostic and Statistical Manual of Mental Disorders, Fifth Edition (DSM-5); (2) Exhibit characteristics of non-suicidal self-injury (NSSI) as defined in the DSM-5; (3) Are aged between 12 and 18 years; (4) Provide voluntary informed consent from the participant, with additional consent from a legal guardian for those under 18; (5) Possess adequate reading comprehension, verbal communication, and writing abilities.

Participants are excluded from the study if they meet any of the following criteria: (1) Have a comorbid psychiatric disorder such as intellectual disability, autism spectrum disorder, or stereotypic movement disorder with self-injury; (2) Have a history or current diagnosis of a central nervous system disease, endocrine disorder, or other severe physical illness; (3) Are currently receiving or have received any form of systematic horticultural therapy within the past three months; (4) Have a known allergic reaction to pollen, soil, or other materials that may be encountered during the intervention; (5) Exhibit acute suicidal risk or behavior requiring immediate clinical intervention.

#### Discontinuation criteria

2.2.3

Participants may be withdrawn or discontinued from the study if any of the following criteria are met: (1) Poor adherence or failure to complete study-specified assessments; (2) Incomplete medical records affecting the evaluation of primary or secondary outcomes; (3) Voluntary withdrawal of informed consent by the participant or their legal guardian; (4) Experiencing significant clinical deterioration, serious complications, or special physiological changes during the study that make continued participation unsuitable; (5) The investigator determines, for other justified reasons, that continued participation is not appropriate.

#### Recruitment

2.2.4

This study plans to recruit 66 adolescent inpatients with MDD and comorbid NSSI at the Affiliated Brain Hospital of Guangzhou Medical University. Trained researchers will conduct an initial screening of potential eligible participants in the system according to the established criteria. Subsequently, the attending physician will review and confirm eligibility based on clinical judgment. Adolescents who meet the inclusion criteria and do not meet any exclusion criteria, along with their guardians, will be invited for a face-to-face interview. During this interview, researchers will provide detailed information and complete the formal informed consent process.

#### Consent procedure

2.2.5

For participants under 18 years of age, written informed consent is obtained from both the adolescent participant and their legal guardian. The consent procedure is conducted one-on-one by a researcher in a quiet and private setting. The researcher provides detailed explanations about the study’s purpose, procedures, potential benefits and risks, confidentiality measures, the principle of voluntary participation, and the right to withdraw. Ample time is ensured for questions and deliberation. Both the participant and the guardian sign the written informed consent form only after fully understanding the information and without any undue influence. This study does not involve the collection of biological samples. All collected data are used solely for the statistical analyses specified in this protocol.

### Randomization and blinding

2.3

This study employs block randomization. An independent researcher (the sequence generator), who is not involved in participant recruitment, intervention delivery, or outcome assessment, uses R software (version 4.5.0) to generate the randomization sequence. The block size is concealed and known only to the sequence generator until the trial concludes. Participants are allocated in a 1:1 ratio to either the intervention group or the control group. After generation, the sequence is sealed in sequentially numbered, opaque, sealed envelopes. The custody and opening of these envelopes are the sole responsibility of another independent researcher (the allocation custodian), who is not involved in sequence generation, recruitment, or assessment. Once a participant meets the inclusion criteria and completes both the informed consent process and the baseline assessment, the allocation custodian opens the corresponding envelope in sequential order. The allocation information is then disclosed to the intervention facilitator, and the participant is assigned to the corresponding group to receive the designated intervention.

This study employs a blinded design. Due to the nature of TH intervention, blinding of participants and intervention facilitators is not technically feasible. However, outcome assessors and data analysts remain blinded to group allocation. To minimize the risk of unblinding due to environmental cues in the closed ward setting, the following measures will be implemented. Outcome assessments will be conducted in a designated room that is physically separate from the intervention area and not used for TH activities. Assessment sessions will be scheduled at times that do not overlap with TH sessions. Participants will be instructed not to disclose their group assignment or discuss TH activities during assessments. If accidental unblinding of an assessor occurs, this will be documented, and a different blinded assessor will complete the remaining assessments for that participant. Communication regarding group allocation between researchers and assessors is strictly prohibited. All assessment forms and study documents identify participants only by a study ID, with no group information included. Final unblinding will occur according to the pre-specified study protocol upon trial completion. Additionally, emergency envelopes containing participant allocation and treatment information are prepared in advance. In the event of a serious adverse event (SAE) where the treating physician must know the specific intervention to provide emergency medical care, and following confirmation by the principal investigator, the emergency unblinding procedure will be initiated immediately in accordance with the protocol, with detailed documentation of the event.

### Interventions

2.4

#### Treatment as usual

2.4.1

This study aims to evaluate whether adding TH to a standardized regimen of treatment as usual (TAU) provides additional benefit. To independently assess the additive effect of TH as an adjunctive therapy, the control group receives two weeks of TAU during the trial period. All TAU is provided according to the hospital’s standard clinical pathways. TAU comprises treatment and usual care. The treatment consists of antidepressant medication, supplemented by physical therapy, psychotherapy, and rehabilitation training. The usual care includes admission orientation, health education on symptoms, consequences and treatment options for depression and NSSI as well as the importance of treatment adherence, medication guidance, discharge planning, and psychological support.

During the study period, the provision of TAU is at the discretion of the attending physician. Participants are not restricted from receiving other treatments or care beyond the designated protocol. To address potential heterogeneity in TAU, the following TAU components will be systematically recorded for all participants throughout the trial: antidepressant medication, including drug name, daily dose, and any dose adjustments; physical therapy, including type, frequency, and duration; psychotherapy, including modality, number of sessions, and duration; and rehabilitation training, including type and frequency. If a participant’s symptoms worsen and require additional treatment, all related details are fully documented in the case report form. These data will be incorporated into the statistical analysis to control for potential confounding effects.

#### Therapeutic horticulture

2.4.2

The intervention group will receive the TH intervention based on the healing system framework, in addition to the TAU received by the control group. Specifically, while receiving the identical two-week regimen of TAU as the control group, the intervention group participates in the additional TH program. The TH is delivered in a group format, with 3 to 6 participants per group. Sessions are conducted in the psychotherapy room of the psychiatric ward at the Affiliated Brain Hospital of Guangzhou Medical University. The intervention lasts for two weeks, comprising four sessions per week, each lasting 60 to 90 minutes. The TH protocol was developed by the research team under the guidance of domain experts, based on the healing system theoretical framework. The detailed intervention protocol is presented in **Table 2**.

**Table 2 T2:** Therapeutic Horticulture intervention program.

Session	Activity	Objective
1	1.1 Sensory Immersion & Ice-breaking	-Enhance interest, encourage self-expression, and promote social interaction.
	1.2 Craft Self-made Grass Head Dolls	-Enhance self-efficacy.
2	2.1 Divide & Plant Greenery	-Alleviate stress, enhance self-efficacy, and promote social interaction.
	2.2 Prepare Homemade Orange Peel Seasoning	-Regulate emotions and enhance self-awareness.
3	3.1 Create Simple Pressed Flowers	-Encourage acceptance of outcomes and recognize the growth potential of appropriate pressure.
	3.2 Creative Leaf Art & Printing	-Externalize emotions and reduce emotional repression.
4	4.1 Cooperative Flower Basket Assembly	-Promote social interaction and enhance self-efficacy.
	4.2 Sensory Discrimination of Flowers	-Relieve stress and facilitate emotional expression.
5	5.1 Herbal Tea Tasting	-Relax the body and mind, and focus on the present.
	5.2 Pot Painting & Decoration	-Promote non-verbal self-expression.
6	6.1 Cooperative Nutrient Soil Preparation	-Relieve stress and reduce social avoidance.
	6.2 Combination Potted Plant Arrangement	-Facilitate the expression of inner emotions.
7	7.1 Create Stamping & Embossing Cards	-Enhance self-efficacy, encourage self-expression, and promote social interaction.
	7.2 Craft Self-made Sachets	-Regulate emotions, enhance self-efficacy.
8	8.1 Plant Harvesting & Tea Preparation	-Enhance positive emotions and boost self-efficacy.
	8.2 Achievement Sharing & Reflection	-Strengthen self-efficacy and hope, reduce loneliness, and foster responsibility and connection.

All plant materials used in this program are pre-selected by the research team based on the healing system framework to ensure consistency of sensory stimuli across activities. The plants include aromatic herbs such as mint, patchouli, and lavender; fresh flowers such as spray roses and sunflowers; foliage plants such as fittonia and miniature coconut palm; and edible plants such as citrus fruits and cherry tomatoes. All materials are screened for non-toxicity and potential allergens prior to use. The same core plant materials are used across all intervention groups to ensure standardization. To foster engagement and a sense of ownership, participants may choose from a limited set of options in certain activities, such as selecting preferred flowers for basket assembly or choosing among herbal tea varieties.

To ensure standardization and safety, the TH facilitators must complete standardized TH training through online courses, academic conferences, and practical workshops. They are permitted to deliver the intervention only after mastering the relevant theory, techniques, and practical skills, and upon passing a competency assessment. The principal investigator will assess and supervise adherence to the intervention protocol. All necessary materials are prepared prior to each session. Each session follows a standardized procedure to ensure safety and consistency. Sessions conclude with a summary and sharing segment, during which participants are encouraged to share their experiences and reflections, and the facilitator addresses any questions. Following the session, all materials are inventoried, recorded, and stored properly.

To enhance participant engagement and adherence, the facilitator provides each participant with an activity stamp card. After each TH session is completed, the facilitator seals the activity stamp card. Participants who collect all eight stamps receive a commemorative certificate and a small gift at the final session. Furthermore, the highlights of the next session are previewed verbally at the end of each meeting. The facilitator also provides a reminder for the upcoming session one day in advance.

Adherence to the TH intervention will be quantified as the proportion of scheduled sessions attended by each participant. Completion of at least six of the eight sessions, corresponding to 75% or more, will be considered adequate adherence. Overall adherence will be reported as the mean proportion of sessions attended across all participants in the intervention group, along with the number and percentage of participants meeting the adequate adherence criterion. An exploratory subgroup analysis will be conducted to examine whether the treatment effect on the primary outcome differs between participants with adequate adherence and those with inadequate adherence.

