### Sample size

2.8

The primary outcome of this study is the NSSI level score of participants. Let n_1_ and n_2_ respectively represent the sample sizes of the intervention group and the control group. The study sets α = 0.05, β = 0.20 (two-sided test), with a statistical power (1-β) of 80%. The sample size ratio between the two groups is n_1_:n_2_ = 1:1. A previous RCT conducted in Chinese adolescents with comorbid MDD and NSSI, the same target population as this study, was referenced; the primary outcome in that trial was also assessed using the ASHS (40). The mean difference between the intervention and control groups was μ_1_ - μ_2_ = 13, with a standard deviation σ = 17.59. Substituting these values into the formula yielded n_1_ = n_2_ ≈ 29. Accounting for an estimated 10% attrition rate, the final calculated sample size is 33 participants per group, resulting in a total of 66 participants for the study.

$$n=\frac{2\;{\left(Z_{1-\alpha /2}+Z_{1-\beta }\right)}^{2}\;\sigma^{2}}{{\left(\mu_{1}-\mu_{2}\right)}^{2}}$$

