Prior to the intervention, baseline characteristics and baseline outcome measures will be compared between the two groups to assess the balance achieved by randomization. Normally distributed continuous variables will be presented as mean ± standard deviation (SD) and compared using the independent samples t-tests. Non-normally distributed continuous variables will be presented as median and interquartile range (Median, IQR) and compared using the Mann-Whitney U test. Categorical variables will be presented as frequency and percentage (n, %) and analyzed using Chi-square test or Fisher’s exact test.

Analysis of Covariance (ANCOVA) will be used to assess the intervention effects. The post-intervention (T_1_) score will serve as the dependent variable, with the group assignment as a fixed factor and the corresponding baseline (T_0_) score included as a covariate in the model. Analysis of Covariance (ANCOVA) will be used to assess the intervention effects. The post-intervention (T_1_) score will serve as the dependent variable, with the group assignment as a fixed factor and the corresponding baseline (T_0_) score included as a covariate in the model. The primary outcome is a single endpoint and is exempt from multiplicity adjustment. To control for inflation of Type I error due to multiple comparisons across the five secondary outcomes, the Benjamini-Hochberg False Discovery Rate (FDR) correction will be applied to the following outcomes as a family: depressive symptoms measured by HAMD-17, alexithymia measured by TAS-20, self-efficacy measured by GSES, sleep quality measured by PSQI, and loneliness measured by UCLA-LS. A Generalized Linear Mixed Model (GLMM) will be used for a secondary analysis of the primary outcome. A Generalized Linear Mixed Model (GLMM) will be used for a secondary analysis of the primary outcome.

A reduction of ≥30% in the NSSI level score from baseline is prespecified as the minimal clinically important difference (MCID). Participants who achieve this reduction are defined as responders, and the responder rate will be compared between groups using the chi-square test or Fisher’s exact test. For all outcomes, effect sizes (Cohen’s d) with 95% confidence intervals will be reported.

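### TH is given in groups of 3 to 6, but the primary ANCOVA and the sample size assume independent participants, so any positive within-group correlation raises the type I error above 5%

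*Protocol article*

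**What the plan says.** **Delivery (section 2.4.2).** "The TH is delivered in a group format, with 3 to 6 participants per group". There are eight sessions over two weeks. Table 2 includes ice-breaking, joint basket assembly and joint soil preparation, and lists social interaction and reduced loneliness among its aims. Each session closes with participants sharing their experiences. Section 2.4.1 leaves treatment as usual to the attending physician and defines no comparable groups.

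**Analysis (section 2.9).** The plan states: "Analysis of Covariance (ANCOVA) will be used to assess the intervention effects". The modelled outcome is the T1 value, and the right-hand side of the model is described as "with the group assignment as a fixed factor and the corresponding baseline (T_0_) score included as a covariate in the model". Three treatment-as-usual covariates are added: number of psychotherapy sessions, antidepressant dose, and receipt of physical therapy. No term for TH group appears. The primary analysis uses multiply imputed data. A generalized linear mixed model is planned as a secondary analysis of the primary outcome, with no random effect named.

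**Sample size (section 2.8).** The inputs come from an earlier trial in the same population: "The mean difference between the intervention and control groups was μ_1_ - μ_2_ = 13, with a standard deviation σ = 17.59". Allocation is equal between the arms, and the calculation is reported thus: "Substituting these values into the formula yielded n_1_ = n_2_ ≈ 29". Allowing for 10% dropout raises this to 33 in each arm, or 66 overall. The formula is the usual one for two independent means, and attrition is the only inflation.

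**The concern.** Participants who go through cooperative and sharing activities together are likely to end with correlated scores, and the intervention works partly through that interaction. A null mean effect does not remove the correlation, since group process can move some groups up and others down. An ANCOVA that treats the TH participants as independent counts more information than there is in that arm. Its standard error is then too small, its confidence interval too narrow, and its test rejects a true null more often than 5% of the time. At stake is the single primary test, judged at P < 0.05, and the bias is towards a false positive. The ANCOVA for the five secondary outcomes, one of which is loneliness, has the same weakness.

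**Working it through.** **Inputs from section 2.8:** difference 13, SD 17.59, two-sided α 0.05, power 80%, 1:1 allocation, 29 per arm before attrition and 33 after. **From section 2.4.2:** group size m from 3 to 6. **Assumed, because the article gives none:** ICC from 0.01 to 0.20, and a mean group size of 4.5 (the midpoint).

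**1. The plan's figure.** n = 2(1.96 + 0.8416)² × 17.59² / 13² = 28.74, so 29 per arm. 29/0.9 = 32.2, so 33 per arm and 66 in total. The figure reproduces exactly. It assumes independent participants and takes no credit for baseline adjustment.

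**2. Number of TH groups.** 33/6 = 5.5 and 33/3 = 11, so about 6 to 11.

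**3. Type I error of the planned test.** With clustering in the TH arm only:
- Design effect in that arm: DE = 1 + (m − 1) × ICC.
- Variance of the difference: (SD²/n)(1 + DE), against 2SD²/n under independence.
- Ratio of true to naive standard error: r = √[(1 + DE)/2].
- Actual two-sided error: 2[1 − Φ(1.96/r)].

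Example at m = 4.5 and ICC 0.05: DE = 1 + 3.5 × 0.05 = 1.175; r = √1.0875 = 1.043; 1.96/1.043 = 1.88; error 6.0%.

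| ICC | DE (m = 4.5) | r | Error, m = 4.5 | Error, m = 3 | Error, m = 6 |
|---|---|---|---|---|---|
| 0.01 | 1.035 | 1.009 | 5.2% | 5.1% | 5.3% |
| 0.05 | 1.175 | 1.043 | 6.0% | 5.6% | 6.5% |
| 0.10 | 1.350 | 1.084 | 7.1% | 6.2% | 8.0% |
| 0.20 | 1.700 | 1.162 | 9.2% | 7.4% | 11.0% |

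Simulation of a naive t-test (30 per arm, 100,000 runs) agrees: 5.6% and 6.5% at ICC 0.05, and 6.1% and 8.0% at ICC 0.10, for groups of 3 and 6. With 7 TH groups the naive error was 5.8% and 6.8% at ICC 0.05 and 0.10. A Satterthwaite test on the TH group means held about 5%.

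**4. Power.** With 29 per arm, m = 4.5 and a normal approximation, power is Φ(13/SE − 1.96) with SE = 17.59 × √[(1 + DE)/29]:
- ICC 0.05: SE = 17.59 × √(2.175/29) = 4.82; 13/4.82 − 1.96 = 0.74; power 77%.
- ICC 0.10: SE = 17.59 × √(2.35/29) = 5.01; 13/5.01 − 1.96 = 0.64; power 74%.

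These figures ignore the few degrees of freedom that about 7 groups provide. By simulation, the Satterthwaite test on the means of 7 TH groups has about 72% power at ICC 0.05 and 69% at ICC 0.10, without baseline adjustment.

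**5. Offset from baseline adjustment.** A baseline to post-score correlation ρ multiplies the variance by 1 − ρ². To cancel the inflation in step 3, ρ must equal √[1 − 2/(1 + DE)]. This is 0.22 (m = 3) to 0.33 (m = 6) at ICC 0.05, and 0.30 to 0.45 at ICC 0.10. At ρ = 0.5 and m = 4.5, the normal approximation gives 88% power at ICC 0.05 (SE = 4.82 × √0.75 = 4.17) and 85% at ICC 0.10 (SE = 5.01 × √0.75 = 4.34). Small-sample degrees of freedom would lower both.

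**The case against.** **The size is unknown.** The article gives no ICC, and at 0.01 the inflation is negligible. Section 2.4.2 standardises training, session procedure and core plant materials, which works against a large ICC. It does not say that each group has its own facilitator or fixed membership, and facilitators who run every group would add no variance between groups. Nor are controls shown to be free of shared influences: treatment as usual includes psychotherapy and rehabilitation of unstated format, and all participants are on one closed ward. All of this stands. It limits the size of the effect, not its direction.

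**Power may be intact.** A reader might infer that a correct analysis must have less than 80% power, and might restate section 2.8 as 74% to 77%. The article supports neither step. Its formula ignores baseline adjustment, and the baseline correlation is as unknown as the ICC, so the sign of the net change is undetermined. If all 33 per arm complete, power under the same normal approximation stays at 80.8% to 83.4% at ICC 0.05 for groups of 6 and 3. The 74% to 77% range also leaves out the small-sample degrees of freedom that a cluster-aware test needs. Neither baseline adjustment nor full retention brings the type I error back to 5%.

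**The mixed model or a fuller plan may deal with it.** The mixed model could carry a TH-group effect, but it is secondary and names none. A fuller analysis plan may exist, although the Ethics and dissemination section says that the plan is presented in this article. Either way, the point is not a missing detail: the primary model is listed term by term, and both it and the sample-size formula assume independence.

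**Conclusion.** The concern holds, conditional on a positive within-group correlation, which the cooperative and sharing format makes plausible. The planned ANCOVA then understates the standard error. At a mean group size of 4.5 the two-sided error is about 5.2%, 6.0%, 7.1% and 9.2% at assumed ICCs of 0.01, 0.05, 0.10 and 0.20. A reader might conclude outright that the stated 5% error and 80% power fail. That goes too far: the first depends on an ICC that nobody has stated, and the second also depends on an unstated baseline correlation. What can be said about power is that 80% with 29 per arm assumes independence and no baseline adjustment. The unadjusted cluster-aware test would have about 72% at ICC 0.05 and 69% at ICC 0.10, and a baseline correlation of about 0.5 could offset much or all of that loss.

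**What to change.** 1. **Data.** Record a TH group identifier for every TH participant in the case report form.
2. **Primary model (section 2.9).** Fit the planned model as a partially nested mixed model: a random intercept for TH group in the TH arm only, controls as singletons, and Satterthwaite or Kenward-Roger degrees of freedom. Keep the planned fixed effects (randomised group, baseline score and the three treatment-as-usual covariates) unless they are changed for other reasons.
3. **Missing data.** Carry TH group through the multiple imputation, and say how the degrees of freedom are handled in pooling.
4. **Sample size (section 2.8).** State that 80% power with 29 per arm assumes independence and no baseline adjustment. Give power over a stated range of ICC and baseline correlation, computed for the cluster-aware test with small-sample degrees of freedom.

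Settle this before unblinding. The cost is one extra field and revised analysis text. Intervals will be slightly wider, and the ICC will be estimated imprecisely from about 6 to 11 groups. The trial should not be enlarged for this.
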